## Abstract

**Background:**

Colorectal cancer is a leading cause of cancer mortality. Screening can be effective but is underutilized. System- or multi-level interventions could be effective at increasing screening, but most have been implemented and evaluated in higher-resource settings such as health maintenance organizations. Given the disparities evident for colorectal cancer and the potential for screening to improve outcomes, there is a need to expand this work to include diverse settings, including those who treat economically disadvantaged patients. This paper describes the study protocol for a trial designed to increase colorectal cancer screening in those ‘safety-net’ health centers that serve underinsured and uninsured patients. This trial was designed and is being implemented using a community-based participatory approach.

**Methods/design:**

We developed a practical clinical cluster-randomized controlled trial. We will recruit 16 community health centers to this trial. This systems-level intervention consists of a menu of evidence-based implementation strategies for increasing colorectal cancer screening. Health centers in the intervention arm then collaborate with the study team to tailor strategies to their own setting in order to maximize fit and acceptability. Data are collected at the organizational level through interviews, and at the provider and patient levels through surveys. Patients complete a survey about their healthcare and screening utilization at baseline, six months, and twelve months.

**Outcomes:**

The primary outcome is colorectal cancer screening by patient self-report, supplemented by a chart-audit in a subsample of patients. Implementation outcomes informed by the Reach, Efficacy/Effectiveness, Adoption, Implementation, and Maintenance (RE-AIM) conceptual framework will be measured at patient, provider, and practice levels.

**Discussion:**

Our study is one of the first to integrate community participatory strategies to a randomized controlled trial in a healthcare setting. The multi-level approach will support the ability of the intervention to affect screening through multiple avenues. The participatory approach will strengthen the chance that implementation strategies will be maintained after study completion and, supports external validity by increasing health center interest and willingness to participate.

**Trial registration:**

NCT01299493

## Background

Colorectal cancer (CRC) is a leading cause of cancer death among men and women in the United States
[1]. Many CRC deaths could be avoided through prevention and early detection activities; early stage CRC is associated with excellent survival
[1]. Routine screening for CRC is recommended starting at age 50 years for adults at average-risk; several different screening tests have been found effective and are recommended at varying intervals
[2,3]. CRC is unique among cancers, because screening is associated not only with early detection, but with prevention
[4]. Cancers can be averted through the identification and removal of precancerous polyps. Yet, colorectal screening is underutilized; at least 40% of age-eligible U.S. adults are not adherent to current screening guidelines
[5,6]. This rate is lower than many other cancer screenings.

There are disparities in screening and survival from CRC. Individuals who are lower income, underinsured or uninsured, or are from a racial/ethnic minority are less likely to get screened and more likely to be diagnosed at later stages
[1,7]. Uninsured patients fare worse than their insured counterparts even when adjusting for stage at diagnosis
[7-12]. Given that CRC is a leading cancer diagnosis and disparately experienced, and that effective prevention and early detection tools reduce mortality by one-half but are under-utilized in routine primary care settings
[13,14], it is important to investigate the feasibility and effectiveness of strategies to increase screening.

Interventions to increase CRC rates that are focused on individual level factors have had only minimal to moderate success in getting patients screened. While individual-level strategies can be effective and have promise, systems- or multi-level approaches have the potential to reach a wider swath of the patient population and thus may have more overall impact
[15-18]. Such approaches can set the stage to increase the likelihood of patient-provider discussion about CRC screening as well as increase the likelihood that screening is referred and completed. Most interventions have been tested in structured and well-resourced settings
[19-22]. In response to a Request for Applications (CA 09–032) from the National Cancer Institute requesting a randomized trial using Community-Based Participatory Research (CBPR) methods, we met with our Colon Cancer Community Advisory Board (CAB) to identify needs and elicit preferences and suggestions for study design and implementation. Our objective in this study is to conduct a practical clinical trial
[23-27] to evaluate the viability and effectiveness of evidence-based implementation strategies in community health centers serving populations disparately affected by CRC. To achieve our stated aims, we are developing, implementing, and evaluating a systems-level intervention aimed at increasing CRC screening. The long-term goal is to reduce CRC disparities by developing sustainable and disseminable implementation approaches that will effectively promote informed decisions about CRC screening across a variety of settings, particularly those considered underserved. Our protocol is described below.

## Methods

This delayed start cluster randomized controlled study is designed as a ‘practical clinical trial’
[23-28]. As such, it is designed to test the impact of an evidence-based intervention under ‘real world’ conditions. Using a rolling recruitment, community health centers (CHCs) are randomized to either intervention or comparison (*i.e.*, delayed intervention). The primary outcome is CRC screening rates as assessed by patient self-report. Other outcomes, such as implementation fidelity and reach, will be evaluated according to the Reach, Efficacy/Effectiveness, Adoption, Implementation, and Maintenance (RE-AIM) conceptual framework
[29-33]. This study underwent review by the Washington University Human Research Protection Office (IRB Protocol #201110005).

### Role of community-based participatory research in this study

Based on the RFA and the input from our CAB, we designed this research to follow established CBPR principles, including acknowledging the community; fostering co-learning and capacity building for all; building on strengths and resources within the community; integrating and achieving a balance of all partners; facilitating collaborative, equitable partnership in all phases of research; a focus on local relevance and determinants of health; involving partners and systems development in a cyclical and iterative process; disseminating finding and knowledge gained to all partners and involving all partners in the dissemination process; and planning for a long-term process and commitment
[34,35]. Key aspects of CBPR incorporated in this trial include collaborative partnership during design, development, implementation, and evaluation, an emphasis on local relevance, and a commitment to long-term relationships and sustainability of interventions. As such, the early outcomes and formative work involved in this research inform the procedures used in the latter activities. Partnered activities and decisions occur throughout the trial. Our cancer center’s Program for the Elimination of Cancer Disparities had an existing network of community and clinical partners who formed our CAB and helped facilitate the integration of CBPR into the proposal development and planning.

### Theoretical framework

In addition to applying CBPR principles, another goal of our study was to incorporate a multi-level approach that acknowledged practical factors related to implementation across settings. We chose the RE-AIM framework
[29-33] as the guide for our measures selection and analysis plan. RE-AIM describes different components of dissemination research and is useful for translating research to practice and for conceptualizing the external validity of a trial. The following RE-AIM concepts are incorporated into our measures and analyses: reach and representativeness, differences in implementation between CHCs, adoption of the trial and of the various evidence-based implementation strategies by CHCs and providers, effectiveness of the overall intervention in increasing screening, and maintenance of resultant strategy changes after the end of data collection. The study aims to reach patient, healthcare providers, and systems that affect care and care provision.

### Setting and participants

#### Community health centers

To be eligible, CHCs must serve mostly Medicaid, uninsured, or lower-income patients; be willing to be randomized to intervention or comparison, and willing to allow the research team access to CHC managers/directors, patients, and providers. Sites (n = 16) are recruited on a rolling basis. We chose this approach in order to better serve the sites’ timetables and availability, and to tap on their enthusiasm for improving quality of care at their sites. Recruiting all sites at the beginning of the trial would force some CHCs to wait before the study started at their site, risking dropout due to administrative turnover or emerging or competing needs of the CHC.

There are over 30 CHCs in our metropolitan region. CHCs were initially identified from amongst our existing community partners. Next, we created a list of federally-qualified CHCs and other known CHCs in our targeted region, and approached them to assess interest. Where possible, we start with a known contact; in other sites, the health center Chief Executive Officer or Chief Medical Officer is identified from websites. In all cases, potential sites are emailed an Institutional Review Board-approved invitation letter and study information sheet. Follow-up is conducted by the study team via email and telephone. In most cases, a combination of email, telephone, and in-person contacts will be made before CHCs formally agree to participate in the trial. With each CHC, we conduct an organizational assessment upon entry and exit into the survey. Additionally, CHC providers will answer anonymous surveys at the start/end of the study to assess their awareness and perception of the trial. Organizational and provider surveys will help us evaluate the RE-AIM constructs of reach, adoption, implementation, and maintenance. We will also be able to better characterize the representativeness (external validity) of our participating sites.

#### Patients

Although the intervention is delivered at the practice-level, primary outcomes of CRC screening will be assessed via self-report from patients. Patient surveys will inform effectiveness and implementation (for example, if educational materials at the clinic reached patients).

A random sample of patients will be recruited from each participating CHC for the survey. Inclusion criteria include: age ≥49, English-speaking, having contact information listed in the medical record, and been seen at the CHC within the last two years. Patients are recruited by mailed invitation letter from the health center about the study and giving them the opportunity to opt out. Study team members will follow-up with all patients who do not opt out. We will aim to collect baseline data from 100 to 110 respondents per clinic where possible. With 70 to 75% retention by 12 months, this will result in adequate power to detect intervention effects. We recognize that some sites may have smaller patient populations and that retaining participants over the course of the 12-month study may be harder when working with underserved populations whose contact information may change during the study period. However, restricting our sample to only health centers with large or stable patient populations would limit external validity.

The study team considered using chart reviews as the primary outcome. However, given the strength of support for the validity of self-reported CRC screening
[36-39], and the difficulty of chart reviews in low-resource settings where electronic medical records may be harder to search, requiring chart reviews would be a barrier to CHC participation and potentially decrease external validity. We will use a chart audit on a subset of sites for further verification of self-report in this population (see section entitled Data collection – Patient-level data).

#### Intervention

The intervention consists of a menu of evidence-based strategies for increasing CRC screening. There are several evidence-based systems interventions to promote CRC screening in primary care, but few
[20] have been tested in underserved populations or in real-world settings. We selected the primary strategies that have evidence for their effectiveness based on the CDC Community Guide to Preventive Services
[40,41] and the American Cancer Society/National Colorectal Cancer Roundtable Toolkit for physicians
[42,43]: routine patient reminders, provider reminders, provider feedback, and structural changes. These changes can reach the multiple levels of patient care including systems, providers, and patients. CHCs randomized to the intervention arm will be presented with the standard ‘menu’ of implementation strategies and will be able to select the strategies they wish to implement for increasing screening. We will partner with individual sites to tailor these strategies into specific interventions that are compatible with their site and perceived as offering advantage over current practices. Comparison CHCs will be offered the menu of strategies at the end of the trial after data collection has ended. All sites receive access to patient education materials.

We chose this ‘menu’ approach for several reasons: data indicate that healthcare providers are more likely to adhere to an intervention if they helped design and select it
[44]; this approach allows sites to decide which strategies are feasible, relevant, and sustainable in their context (*e.g.*, provider feedback might be difficult in a CHC without electronic records or with basic electronic systems; patient reminders are challenging if patient contact information is not reliable); offering choice enhances generalizability and representativeness by encouraging more wide-spread participation and buy-in by CHCs; and important to our CBPR approach, our community and clinical partners strongly felt that CHCs need to have an active role in selecting the intervention, rather than being ‘told what to do’ by the researchers.

Once decision makers and stakeholders at a HC are identified, the study team will meet with them to discuss their site’s challenges (and current practices) regarding CRC screening, and discuss the general main implementation strategies (reminders, feedback, etc.). Through discussion and consensus, the research team will then develop a menu tailored to each site that is then presented back to the same group for their final decisions. Additional personnel from the CHC will be consulted as needed (*e.g.*, Information Technology officers if a strategy involves the electronic medical record; health center managers if strategies are directed at patients, etc.).

#### Data collection

Our primary outcome will be CRC screening (percent of patients up-to-date on CRC screening per the U.S. Preventive Services Guidelines
[45]) based on a survey of patients age-eligible for screening at baseline, six months, and twelve months. As we will describe, data are also collected at the provider- and practice-level.

#### Patient-level data

The baseline survey will include: demographics, healthcare utilization, medical home, cancer screening, literacy
[46], behavior intentions, barriers to CRC screening
[47-49], and knowledge about colon cancer. Standard measures from national surveys are used as available. The six-month and 12-month surveys include self-reported CRC screening, healthcare utilization, and awareness of screening or educational efforts. CHCs may add site-specific questions if they wish.

#### Recruitment for the patient survey

Procedures for patient recruitment will be finalized in collaboration with the participating sites. At most sites, the research team will work with the CHC to randomly select eligible patients and mail letters of invitation to potential participants. Letters will have an opt-out option and will be followed up by telephone. We expect that some sites will not want to mail letters out due to privacy concerns. In those cases, participants will be recruited in person at the participating health center. We will track the type of recruitment used and evaluate any potential impact or differences.

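### The patient sample is called random at every centre, but some centres will recruit in person; settle the recruitment mode before allocation and prespecify how the analysis handles it

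*Protocol article*

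**What the plan says.** The Patients section makes an unqualified statement about the sample that carries the primary outcome: "A random sample of patients will be recruited from each participating CHC for the survey". It gives one route of approach: "Patients are recruited by mailed invitation letter from the health center about the study and giving them the opportunity to opt out".

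The section headed Recruitment for the patient survey is narrower. Random selection with mailing is the procedure for most sites: "At most sites, the research team will work with the CHC to randomly select eligible patients and mail letters of invitation to potential participants". It then foresees exceptions: "We expect that some sites will not want to mail letters out due to privacy concerns". For those sites the alternative is: "In those cases, participants will be recruited in person at the participating health center". The choice is made centre by centre: "Procedures for patient recruitment will be finalized in collaboration with the participating sites". One safeguard is stated: "We will track the type of recruitment used and evaluate any potential impact or differences".

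Allocation is by centre: "community health centers (CHCs) are randomized to either intervention or comparison", on a rolling basis, with 16 sites. The Analysis section specifies a generalized linear mixed model with individual-level and cluster-level covariates. Candidate variables are tested one at a time against the outcome, and those that reach significance are considered for the adjusted model.

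**The concern.** The two sections cannot both be right. A list of everyone seen in the last two years and the people present at the centre during recruitment are different sampling frames, and the second over-represents frequent attenders. Attenders may differ in baseline screening. The Discussion also says that patients meet the intervention if and when they have an appointment, so attenders may be more exposed to it. The documents give no figure for either difference.

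Mode follows a centre's preference and is fixed within that centre, so there are at most 16 observations on it. If in-person centres fall unevenly between arms, the contrast in screening rates carries part of the difference in who was sampled. What is at stake is a chance distortion of the primary comparison that the stated safeguard is poorly placed to detect, plus a published sampling claim that does not hold at every site.

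**Working it through.** **The plan's own figure (context only; the point does not turn on it).** From the Power section: 16 centres, 74 per centre, ICC 0.04, 80% power for 15 points. Design effect = 1 + (74 − 1) × 0.04 = 3.92. With 8 centres per arm, 8 × 74 = 592 patients, and 592 / 3.92 = 151 effective patients per arm. Assuming two-sided 5% and a pooled z-test, power is 0.798 for 25% vs 40% or 60% vs 75%, and 0.745 for 40% vs 55%. The stated 80% is reproduced at some control rates; the article does not give the control rate.

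**Chance imbalance of mode.** Assumptions: 4 of 16 centres recruit in person, allocation is 8:8, mode is independent of arm. The article gives neither the number of in-person centres nor the ratio. The number in the intervention arm is hypergeometric:

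- Balanced 2-2: C(4,2) × C(12,6) / C(16,8) = 6 × 924 / 12870 = 0.431.
- Imbalance of two or more sites (3-1 or 4-0, either direction): 1 − 0.431 = 0.569.
- 4-0 in either direction: 2 × C(12,4) / 12870 = 2 × 495 / 12870 = 0.077.

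**Size of the shift.** Let D be the assumed difference in up-to-date rate between in-person and mailed samples, and a and b the in-person centres in the two arms. With equal centre sizes, the unadjusted shift is D × (a − b) / 8.

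| D (assumed) | 3-1 split | 4-0 split |
|---|---|---|
| 5 points | 1.25 | 2.5 |
| 10 points | 2.5 | 5.0 |
| 15 points | 3.75 | 7.5 |

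For scale, the target difference is 15 points. The standard error of the arm contrast is √(2 × p(1 − p) / 151), which is 5.3 points at p = 0.3 and 5.8 at p = 0.5.

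**Power of the planned evaluation of mode.** Compare 4 in-person with 12 mailed centres, ICC 0.04 and 74 per centre, two-sided 5%, t with 14 df (test and level assumed). The variance of a centre mean is p(1 − p) × 3.92 / 74. At p = 0.5 this is 0.25 × 3.92 / 74 = 0.01324. The standard error of the mode difference is √(0.01324 × (1/4 + 1/12)) = 0.0664. For a 10-point difference the noncentrality is 0.10 / 0.0664 = 1.51 and power is 0.29. Over rates of 30% to 60%, power is 0.29 to 0.33; with 3 to 5 in-person centres it is 0.24 to 0.37.

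**Consequence under the covariate rule.** If the screening test respects clustering, a real 10-point mode effect fails to reach significance about 7 times in 10 and is left out. A test that ignored clustering would flag mode more often, but with an inflated false-positive rate, so it would not be a sound basis for the decision either.

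**The case against.** Several parts of the opposing case stand.

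- **Confounding with centre is not confounding with arm.** Centres are randomised, and the stated reason for in-person recruitment is a site's privacy concern, not its arm. If mode does not depend on arm, expected bias is zero. What remains is chance imbalance and extra between-centre variance, which a clustered analysis largely carries in its standard error. A 2.5-point shift is under half a standard error.
- **Mode is not inestimable.** Arm is also constant within a centre and is estimated. The evaluation of mode has low power, not none.
- **Baseline data help.** Baseline screening and healthcare utilization are collected on the same patients, and adjusting for them would remove part of the shift. The Analysis section does not guarantee that they enter the model, because they too must pass the screen, though baseline screening would very likely pass.
- **The size is assumed.** The gap between modes, the number of in-person centres and their split have no source in the documents.
- **The manner of in-person approach is not described.** Calling it convenience sampling would be the reader's inference. Even a consecutive approach, however, samples attenders and not the two-year list.

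A reader might also infer selection after allocation: that staff who know the arm could choose whom to approach on site. The article does not support this. It gives neither the order of patient enrolment and allocation nor what recruiters know, and a condensed article may leave both to the full protocol.

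Flexibility for sites is deliberate in a practical trial. It justifies allowing two modes; it does not make the unqualified sampling statement correct or the handling of mode adequate.

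**Conclusion.** The point holds in limited form. The two sections conflict: the sample is random only where a list is sampled, and sample type is a centre-level attribute. No systematic bias is shown. Under the assumptions of 4 in-person centres, 8:8 allocation and mode independent of arm, imbalance of two or more sites is more likely than not (0.57), and the extreme 4-0 split is uncommon (0.077). For an assumed 5 to 15 point difference between modes, a 3-1 split moves the contrast by 1.25 to 3.75 points before baseline adjustment. That is modest against the 15-point target but worth preventing, because the planned evaluation has only about 30% power at 10 points and the significance screen would often leave a real effect unadjusted. Whether baseline enrolment precedes disclosure of allocation is a matter to confirm, not a fault found.

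**What to change.** 1. Amend the Patients section to say that the sample is random only in list-sampled centres, and that some centres recruit in person.
2. Settle and record each remaining centre's recruitment mode before that centre is allocated. Trial status says only the first set of centres has been recruited, so this is still possible. For centres already enrolled, record the mode used.
3. Either balance the remaining allocations on mode, or prespecify mode as a centre-level covariate together with baseline screening status, which is already collected. Exempt both from the significance screen in the Analysis section.
4. Confirm, from the full protocol or site procedures, that baseline enrolment at a centre precedes disclosure of its allocation.

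The cost is one centre-level degree of freedom if mode enters the model, and the ordering of start-up steps. No new data collection is needed.
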